## Economic Evaluation Model

The purpose of this project is to develop a CVD model which can be used to estimate the health and economic consequences of cardiovascular prevention interventions in the South African population and in high-risk subpopulations. The model will incorporate risk factors and natural history data on ischemic heart disease (angina, myocardial infarction, and sudden cardiac death) and stroke, and will draw upon primary data from the 1998 Demographic Health Study, Statistics South Africa as well as data from the published literature and publicly available databases. With this model, it will be possible to perform cost-effectiveness analyses of CVD management and prevention interventions which incorporate long-term health and economic consequences of CVD prevention, including gains in life expectancy and savings of health care costs.

Such a model will also permit policy makers at the national level to forecast the national impacts of preventive interventions on future CVD incidence rates, CVD mortality, total mortality, and total medical care costs. Such forecasts can help to set priorities for research and development of preventive strategies, by identifying those areas where effective prevention would deliver the most “bang for the buck”.

### Background and Significance

Limited resources for both health care and prevention force choices to be made under strict budgetary limits. Not every promising CVD prevention program can be implemented to the desired extent. Public health departments operating with fixed budgets are forced to set priorities among preventive services, and among primary prevention, early detection, and clinical treatment. Furthermore, it is unrealistic to expect most prevention or intervention studies to follow subjects long enough or in sufficient numbers to reveal the lifetime costs and consequences in terms of survival, quality of life, and lifetime medical costs, let alone disease incidence. As a result, simulation models are needed in order to project the implications, at both the individual and societal levels, of changes in risk factors. Such computer models would build upon available data on the associations between CVD risk factors and CVD incidence, the prevalence of risk factors in the population, the natural and treated history of disease, and the effects of CVD on survival, quality of life, and medical care cost.

The purpose of the cost effectiveness analysis (CEA) in health is to compare the relative value of different options in improving the quality or length of life. The result of such an analysis is usually presented as a ratio (cost/health outcome). The denominator is some improvement in health such as years of life gained or heart attacks prevented. The numerator reflects the costs to achieve the health gain. No specific consensus on acceptable or appropriate cost per health unit gained has been made. However, the Commission on Macroeconomics and Health (WHO, 2001) has suggested that acceptable cost-effectiveness ratios might be around 2- 3 times the GDP per capita. Nonetheless, even without consensus on a threshold for tolerable costs, CEA allows for choices to be made that maximize a health benefit for a given expenditure.

### Preliminary studies

Recently, the South African Hypertension Society adopted and revised its new guidelines [based on the JNC VI and VII guidelines]. As South Africa is a multi-ethnic country where epidemiologic and cost data were available, we therefore felt this provided a unique and timely opportunity to conduct a cost-effectiveness analysis comparing the two approaches to help inform the potential consequences of the various guideline choices for hypertension. The study compared six strategies for different thresholds for the initiation of drug treatment—two different blood pressure levels (160/95 and 140/90 mm Hg taken from the past and the newly proposed South African guidelines respectively), and four different levels of absolute CVD risk over 10 years (40%, 30%, 20% and 15% calculated using the Framingham risk function). All six of these strategies were also compared to one of no primary prevention treatment.

The results of this analysis which we previously showed as preliminary were published in *Circulation* (Gaziano, 2005). The four “absolute risk” strategies had the four lowest incremental cost-effectiveness ratios. The strategy of initiating antihypertensive therapy for those individuals with a predicted 10-year CVD risk > 40% had an incremental cost-effective (C/E) ratio of $700 per quality-adjusted year of life gained compared to no treatment. The “absolute risk of CVD > 30%”, “absolute risk of CVD > 20%” and “absolute risk of CVD > 15%” had C/E ratios of $1600, $4900, and $11,000 per QALY respectively. On the other hand both the 1995 South African guidelines and the new guidelines were more costly and resulted in fewer gains in quality adjusted life-expectancy than the “absolute risk of CVD > 15%” strategy, and were thus dominated by the less costly absolute risk treatment strategies in the cost-effectiveness analysis.

Table 2 compares the projections of morbidity and mortality from our model with the estimates from the available literature on South Africa. In general, the model was able to accurately project the number of deaths due to ischemic heart disease and stroke, the incidence of stroke and the overall direct cost of CVD.

| **Table 2. CVD Model Predicted and Actual Outcomes in South Africa** | | |
| --- | --- | --- |
| Outcome | Model Prediction | Published Reports (range) |
| Annual Death due to IHD | 12% | 5-13% |
| Annual Death due to Stroke | 14% | 8-16% |
| Stroke rate (per 100 000) | 323 | 100-500 |
| Annual Direct Cost of CVD ($US millions) | 690 | 620-810 |

### Overview

The end product of this research will be a set of specifications for a CVD Prevention Policy Model, incorporating CVD risk factors, ischemic heart disease, and stroke. The model design will be population-based for the South African population, which means that it will be able to project numbers of cases prevented, detected, and treated, as well as national CVD mortality, morbidity, and cost, attributable to interventions. It will also be designed to facilitate cost-effectiveness analyses of preventive interventions for which data on risk-factor modification and program cost have been obtained.

**Base case**

Since the goal of our study is to evaluate primary prevention strategies, the simulation will begin with a population over the age of 35 and free of CVD. The base case for comparison in the primary cost-effectiveness analysis will be conducted from a societal perspective data and will look at standard care in South Africa for CVD. The US Panel on Cost-effectiveness in Health and Medicine wrote a textbook on cost-effectiveness methodology. The panel’s recommendations are a consensus of experts on how to conduct and report a CEA using consistent methodologies (Gold, 1996). These recommendations were also adopted by the Disease Control Priorities Project in Developing Countries (DCP2) textbook outlining cost-effective strategies for disease control in developing countries (Jamison, 2006). This textbook was co-sponsored by the WHO, the World Bank, and the Fogarty International Center and funded by the Bill and Melinda Gates Foundation. We will adhere to those recommendations in our analyses.

**Study design**

State-transition simulation models, also called Markov models, will be developed to assess the cost-effectiveness of the integrated care guidelines for CVD to compare to the base case. The model will be programmed in Excel. We will begin with the model for South Africa where we already have some experience and data for input. Once this model is completed, we will be able to build a similar model for Tanzania changing the inputs derived from the epidemiological data in Tanzania. Effects will be measured in life years saved, QALYs and DALYs. Incremental cost-effectiveness (C/E) ratios will be calculated for each of the 3 strategies compared to the base case under consideration. All costs and benefits are discounted at 3% per year consistent with current guidelines.

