To calibrate the risk score previously developed in the NHEFS cohort, we propose to use the South African Demographic Health Survey of 1998 (or Western Cape data) and the CVD morbidity and death rates from Central Statistics South Africa from 2003 and 2008 to recalibrate our lab-based screening tool for five and ten year predictions. We included the following risk factors in our analysis to compare a lab-based tool to a non-lab based tool, using the value closest to the entry date to the cohort for each patient: age (in single years); gender (men v women); smoking status (current smoker, non-smoker—including former smoker); systolic blood pressure (continuous); ratio of low density lipoprotein cholesterol to high density lipoprotein levels (continuous); body mass index (continuous); current prescription of at least one antihypertensive (yes or no), and diabetes status (yes or no). All data for this analysis is based on de-identified data sets. We will also use the DHS 98 and the relevant census data for validation of the WHO risk charts, using information on age, gender, smoking, blood pressure, and reported diabetes status.

The 1998 South Africa Demographic and Health Survey (SADHS) is the first survey of its kind to be carried out in South Africa since the 1994 democratic national elections. This national cross-sectional study collected information on adult health conditions; sexual, reproductive and women’s health; maternal and child health; adult, maternal, child and infant mortality; fertility and contraceptive use. Preparations for the study started in 1995 and the fieldwork was carried out between late January and September 1998.

They were also asked about recent contact with the health-care system, insurance status, family medical history, personal medical history, other medication use, smoking, occupational health, and lifestyle/habits. Information regarding other demographic factors such as age, education level and population group was also recorded.

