**Model Structure**

**Disease Model**

A decision analytic Markov model comparing the two different strategies of care for the care of patients with risk factors for or advanced CVD: standard care and guideline based case management will be built. A Markov model simulates transitions between distinct health states that would occur over a lifetime in a cohort of patients undergoing a selected intervention strategy. Mortality and morbidity data derived from published literature will be used to derive the model probabilities, and costs from the study and project events will tabulated and the outcome for each strategy will be quantified in terms of costs per quality-adjusted life year (QALY) gained.

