**Data Collection**

In each model the adult population will be defined according to age, sex, tobacco status, and BMI in the low cost strategy and age, sex, tobacco status, cholesterol, and diabetes status in the high cost screening strategy. Growing on the experience from evaluating the prevalence, distribution, and medications patterns of hypertension in South Africa, (Steyn *et al*, 2001) we will use the Demographic and Health Survey (DHS) of South Africa to determine the smoking rates, body mass index, and family history of CVD. Estimates on diabetes status and cholesterol levels will be pulled from smaller representative studies (Levitt *et al* 1993, 1999) or our new pilot data since this information was not collected in the DHS. We will use the Statistics South Africa’s database available in the public domain to determine the population by age deciles in South Africa. Utility weights will come from EQ-5D results from the above integrated care guideline as well as other local and international sources.

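### The economic model's stated ratios, for three unnamed strategies, are all against the base case; no between-strategy or dominance rule is given, and sections disagree on strategies and population

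*Combined protocol and SAP*

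**What the plan says.** All references are to the combined protocol and SAP, mostly its Economic Evaluation Model chapter.

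- **Comparator.** Study design: "Incremental cost-effectiveness (C/E) ratios will be calculated for each of the 3 strategies compared to the base case under consideration". Under Base case, the comparison "will look at standard care in South Africa for CVD". The Sensitivity Analysis section varies inputs one at a time and then probabilistically. It adds no comparison between strategies.
- **Number of strategies.** Study design has three, unnamed. Disease Model describes a model "comparing the two different strategies of care for the care of patients with risk factors for or advanced CVD" and names standard care and guideline-based case management. Data Collection refers to a low-cost strategy and a high-cost screening strategy, and Costs counts the blood tests used in screening.
- **Population.** Base case: "the simulation will begin with a population over the age of 35 and free of CVD". Disease Model includes people with advanced CVD, and Community Population splits those with prior CVD into angina, MI and stroke groups.
- **Variables.** Data Collection defines the modelled adults by "age, sex, tobacco status, and BMI in the low cost strategy and age, sex, tobacco status, cholesterol, and diabetes status in the high cost" one. In the validation study, Proposed Model Calibration Approach and Risk Prediction Validation both give a longer list that adds systolic blood pressure and ends with "current prescription of at least one antihypertensive (yes or no), and diabetes status (yes or no").
- **Aim.** The Synopsis says the model serves a comparison of different screening and intervention strategies. The validation study's Background and Significance wants to find the most cost-effective and practical way to screen.

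**The concern.** With one alternative to standard care, a ratio against standard care is the incremental ratio. With several competing alternatives it is not. A decision-maker then needs to know what each extra outlay buys over the next less costly option worth considering. A ratio against a shared base credits a costlier strategy with gains that a cheaper one already delivers, so a strategy that adds cost and nothing else can still fall under an acceptability threshold. The rule in Study design therefore does not answer the plan's own question about which strategy is best.

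The inconsistencies make this worse. Until the strategies, the starting population and the screening variables are fixed, each could be settled after model results are seen.

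**Working it through.** **1. Is there a figure to reproduce?** Study design states a rule and no number, so there is none.

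**2. Counting strategies.**

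| Section | Strategies | Non-base strategies |
|---|---|---|
| Study design | 3, each against the base case | 3 as written (2 if the base case is counted among them) |
| Disease Model | 2, one being standard care | 1 |
| Data Collection | low-cost and high-cost screening | 2, neither mentioned in Disease Model |

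Under the Disease Model count, the Study design rule is adequate. Under either of the others, it leaves out the between-strategy comparison.

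**3. The mechanism.** Let strategy A cost C and gain E against the base, with ratio r = C/E. Let strategy B cost C(1 + s) and gain E(1 + g).

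- B against base = r(1 + s)/(1 + g).
- B against A = r·s/g. If g = 0 and s > 0, B is dominated.

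**4. Illustration.** The documents give no costs or effects for the planned strategies. Assumed for scale: r = 700, 1,600 or 4,900 dollars per QALY, and a ceiling of 11,000, all borrowed from the ratios in Preliminary studies; s from 10% to 100%; g from 0 to 1%. The plan's own threshold of 2 to 3 times GDP per capita cannot be used, because no GDP figure is given.

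| r | B against base, g = 0, s = 10% to 100% | Extra cost s at which B reaches 11,000 against base (11,000/r − 1) |
|---|---|---|
| 700 | 770 to 1,400 | 1,471% |
| 1,600 | 1,760 to 3,200 | 588% |
| 4,900 | 5,390 to 9,800 | 124% |

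Every ratio in the middle column is under the assumed ceiling, yet B buys nothing over A.

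With a small gain, B against A runs from 700 × 0.10/0.01 = 7,000 to 4,900 × 1.00/0.005 = 980,000. The lowest value is under the ceiling, so next-best ranking does not always reject B. The gain at which B becomes acceptable over A is g = r·s/11,000, from 700 × 0.10/11,000 = 0.64% to 4,900 × 1.00/11,000 = 44.5%.

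**5. Is a near-zero gain plausible?** For women in a US cohort, Background and Significance gives C-statistics of 0.829 (lab-based) and 0.831 (non-lab), with chi-square 2.476. On 1 degree of freedom that gives p = 0.1156, matching the stated 0.116. This makes a small gain from laboratory testing a scenario worth planning for. It does not measure that gain.

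**6. Variables.** The validation list is age, sex, smoking, systolic blood pressure, LDL/HDL ratio, BMI, antihypertensive prescription and diabetes. Against it, Data Collection has systolic pressure and antihypertensive use in neither strategy, BMI only in the low-cost one and diabetes only in the high-cost one. The validation list is a single merged list and is not divided into lab and non-lab sets.

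**7. Population.** A cohort free of CVD cannot also contain people entering with angina, MI or stroke. The trial criteria do not exclude prior cardiovascular events; only the validation study does. Trial patients with CVD therefore need a stated place in the model.

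**The case against.** The best defence is that nothing rules out between-strategy ratios. Base case follows an expert panel's recommendations and says "We will adhere to those recommendations in our analyses". Preliminary studies shows that the team's previous South African model reported incremental ratios and discarded dominated strategies. Both points suggest competence and intent. But the documents do not say what the panel recommends on comparators, and a general commitment does not displace the specific comparator written in Study design.

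Four stronger readings are tempting, and the documents do not support them.

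- *That a lab-based arm is one of the three strategies.* Data Collection and Costs make this a fair inference, but the three are unnamed. If Disease Model's wording, "comparing the two different strategies of care", governs, no dominance problem arises.
- *That the model cannot show whether laboratory testing is worth its cost.* If costs and effects are computed for every strategy, the increments follow by subtraction. The fault lies in the stated reporting rule.
- *That laboratory testing adds about nothing.* The C-statistics come from a US cohort, and similar discrimination does not imply equal QALYs. Research procedures and data collection itself notes a lipid ratio in the target areas that differs from Caucasian populations.
- *That the model would evaluate tools other than the validated ones.* The Data Collection sentence may describe how the population is stratified, and the chapter does use blood-pressure change to drive event risk. The mismatch needs clarifying, no more.

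On population, the two descriptions may be two intended analyses. The text does not say so.

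**Conclusion.** The point stands in a conditional form. Study design states a comparator that is wrong for several competing strategies, and it does not serve the aims in the Synopsis and in Background and Significance. Whether it would mislead depends on there being more than one non-base strategy, which the text suggests but does not settle. The conflicts over the number of strategies and the starting population are plain on the page and need no assumption. The dollar results rest wholly on the assumed inputs: within them a dominated strategy can look acceptable, but at a high enough extra cost the ratio against the base would fail too. The error is possible, not certain. It should be corrected. It concerns the economic model alone and leaves the trial's primary analysis and sample size untouched.

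**What to change.** - **Study design:** name every strategy. Rank them by cost and remove those that are dominated or extended-dominated (beaten by a mix of two others). Report each ratio against the next less costly strategy that remains. Keep the ratio against standard care as a supplementary result.
- **Disease Model and Data Collection:** use the same strategies, with the same names and count.
- **Base case, Disease Model and Community Population:** state one base-case population, or label the primary-prevention and prior-CVD analyses as separate.
- **Data Collection:** reconcile the variables with the tools under validation. First split the merged list in Proposed Model Calibration Approach and Risk Prediction Validation into its lab and non-lab sets. Then say how systolic blood pressure and antihypertensive use enter each strategy.

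The cost is wording and a re-sort of model output. No new data are needed.

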**Model Structure**

**Disease Model**

A decision analytic Markov model comparing the two different strategies of care for the care of patients with risk factors for or advanced CVD: standard care and guideline based case management will be built. A Markov model simulates transitions between distinct health states that would occur over a lifetime in a cohort of patients undergoing a selected intervention strategy. Mortality and morbidity data derived from published literature will be used to derive the model probabilities, and costs from the study and project events will tabulated and the outcome for each strategy will be quantified in terms of costs per quality-adjusted life year (QALY) gained.

**Community Population**

The model will incorporate the baseline demographics and estimates from the clinical sites to determine the mean age and risk factor profile for the study populations at baseline. Methodology to collect this information is described below. Using this information we can than predict the likelihood of future vascular events including stroke, fatal and non fatal MI, and the need for hospitalization. For those with prior CVD we will further subdivide the population into the various groups of patients entering into the study: angina, MI, or stroke. Since these three groups have different probabilities of future events we will model them separately and aggregate their costs and benefits over the whole population in proportion to their makeup in the study population.

### Model Structure

The programme will use a decision analytic Markov model built in Excel to model the course of the study population beyond the time of the trial until their death. The time horizon would be for the remaining life of the cohort assuming that the case management system would remain in place. Different assumptions, however, could be made regarding how long differences between the two intervention arms would persist if the case management intervention were withdrawn or if changes in risk factors would reverse if the intensity of the intervention were diminished. These different assumptions will be addressed in sensitivity analyses.

Each year the study population faces a risk of having a cardiovascular disease event (myocardial infarction, cardiac arrest, angina, or stroke), requiring an intervention (angioplasty or surgery), or dying from a CVD or non-CVD related cause as outlined in the figure below. It is recognized that the invasive interventions are used at a much lower rate than in the developed countries. We will then use the study information regarding improvements in the various risk factors such as reductions in blood pressure, changes in the lipid profile, use of medications such as aspirin, and smoking rates to model relative risk differences in the likelihood of events over time based on changes in these risk factors or treatments.

